## Abstract

**Introduction:**

Nearly 90% of all deaths in the Republic of Moldova are caused by non-communicable diseases, the majority of which (55%) are caused by cardiovascular diseases (CVD). In addition to reducing premature mortality from CVD, it is estimated that strengthening primary healthcare could cut the number of hypertension-related hospital admissions and diabetes-related hospitalisations in half. The aim of this evaluation is to determine the feasibility of implementing and evaluating essential interventions for the prevention of CVD in primary healthcare in the Republic of Moldova, with a view towards national scale-up.

**Methods and analysis:**

A national steering group including international experts will be convened to adapt WHO Package of Essential NCD Intervention from Primary Healthcare in Low Resource Settings protocols 1 and 2 to the health system of the Republic of Moldova, develop and conduct training of primary healthcare workers and test a core set of indicators to monitor the quality of care and change in clinical practice. To evaluate the impact of this pilot implementation, a pragmatic, sequential mixed methods explanatory design, composed of quantitative and qualitative strands of equal weight, will be used. Twenty primary healthcare centres will be selected and randomised to the training and implementation arm (n=10) and the usual care arm (n=10). At baseline and 12 months follow-up, a standardised data collection form will be piloted to extract data directly from patient paper records in order to estimate the change in clinical practice. Semi-structured interviews and interclinic peer workshops will be conducted at 12 months follow-up, and qualitative data collected from these formats will be analysed thematically for explanatory themes that relate to the quantitative findings.

**Ethics and dissemination:**

Ethical review and approval has been obtained. Findings of the evaluation will be shared in a project report to key stakeholders, presented back to participants and written into a manuscript for an open access peer-reviewed scientific journal.

Strengths and limitations of this studyTo our knowledge, this is the first description of adapting and piloting WHO essential non-communicable disease interventions in primary healthcare in a low-income or middle-income country and provides a methodological example to other jurisdictions.A mixed methods design allows for a greater understanding of the potential barriers and facilitators to implementation and can inform future health systems development.Primary healthcare facilities will be selected from different regions of the Republic of Moldova in order to pilot implementation in a variety of contexts throughout the country.Since this is an evaluation of a pilot implementation, the sample size is based on pragmatism and not statistical power.We are unable to include patient perspectives and experience in the evaluation, which is an important aspect of healthcare quality.

## Introduction

Globally, non-communicable diseases (NCDs) account for more than one-half of the global burden of disease.^1^ In 2016, an estimated 41 million deaths were due to NCDs, of which nearly half were due to cardiovascular diseases (CVD).^2^ Primary healthcare systems play an important role in the prevention, early detection and appropriate management of these diseases, but many nations lack primary healthcare capacity.^3 4^

To support national governments to realise their commitments in reducing the burden of NCDs, as agreed in the United Nations Political Declaration on NCDs, the World Health Assembly endorsed the WHO Global Action Plan for the Prevention and Control of NCDs 2013–2020. To support implementation of this Action Plan, WHO has identified a set of cost-effective policy options (‘best buys’) for the prevention and control of NCDs within countries.^5^

The Republic of Moldova (henceforth ‘MDA’) is located in Eastern Europe, between Ukraine and Romania; the Capital and largest city is Chisinau. By gross domestic product per capita, MDA is one of the poorest countries in the WHO European Region and it is estimated that 21.9% of citizens live below the absolute poverty line of US$1 per day.^6^

### Non-communicable diseases are a leading cause of death in MDA

While NCDs are a global epidemic, MDA ranks among the countries most affected. Nearly 90% of all deaths in MDA are caused by NCDs, the majority of which (55%) are caused by CVD.^7^ In 2016, the probability of dying prematurely from any of the four major NCDs (CVDs, cancer, diabetes, chronic respiratory disease) was 24.9%; almost twice as high for men (33.7%) as women (17.3%).^8^ Men and people residing in rural areas are disproportionally impacted by CVD and represent key populations for public health intervention.^7^

This burden is driven by some of the highest rates of NCD risk factors, including tobacco and alcohol use, in the WHO European region indicated by a 2013 Stepwise Appraoch to Surveillance (STEPS) survey.^9^ One in four (25.3%) Moldovans smoke tobacco and this rate nearly doubles in men.^9^ Among adults aged 18–69 years, 61.9% currently consume alcohol and one in five people have engaged in heavy episodic drinking (six or more drinks on any one occasion in the past 30 days).^9^

The overall prevalence of obesity among adults is 22.9%, being higher among women (28.5%) as compared with men (17.8%).^9^ The prevalence of raised blood pressure (defined as systolic blood pressure ≥140 mm Hg and/or diastolic blood pressure ≥90 mm Hg or currently taking medication for raised blood pressure) among MDA’s adult population is 39.8%, and 76.2% of these patients are not on blood pressure-lowering medication.^9^ A total of 12.3% of the population have a blood glucose level of ≥6.1 mmol/L, and 29.4% of the population has a total blood cholesterol level of ≥5 mmol/L.^9^ It is estimated that one in five (23.0%) people aged 40–69 years have a 10-year fatal or non-fatal CVD risk of over 30% (including those with an existing CVD).^9^

### Primary healthcare in MDA and commitment to NCDs

According to the Constitution of MDA of 1994, citizens are entitled to a free of charge minimum package of essential health services, including primary healthcare. However, resource constraints have made it difficult to offer these services and significant gaps in care exist.^10^ According to the most recent data (2010), there were 5.3 family doctors per 10 000 inhabitants and 25.9 specialist doctors per 10 000 inhabitants. In rural areas these rates are halved, leading to human resource shortages in primary care.^10^ Approximately 17% of practising physicians in MDA work in primary healthcare, and 92% of them rely on paper-based clinical records.^6^ The most recent estimate (2009) states that there are approximately 630 primary healthcare centres throughout the country, or 21.2 centres per 100 000 people.^6^

Despite these health system challenges, the Government of MDA is committed to improving primary healthcare capacity for NCDs. It is estimated that 60% of hypertension-related hospital admissions (about 12 000 annually) and 40% of diabetes-related hospitalisations (about 5000 annually) could be prevented through strengthened primary healthcare for these conditions, including better identification and management of those at increased CVD risk.^11^

Given the need and international policy support for addressing this gap in NCD care, there was a favourable window of opportunity to act with impact. As such, strengthening primary healthcare was set out as one of the main commitments in the Action Programme of the Government of MDA 2016–2018.^12^ To do this requires the development of simplified clinical protocols, in-person training programmes for nurses and doctors and a core set of indicators to monitor and evaluate changes in the quality of care.

### Essential interventions to prevent cardiovascular diseases in primary healthcare

In order to build capacity in primary healthcare and ultimately prevent premature mortality from CVD in MDA, a study was envisioned to adapt and pilot the WHO Package of Essential NCD Intervention from Primary Healthcare in Low Resource Settings (WHO PEN).^3^ WHO PEN includes simplified clinical protocols which together cover the integrated management of hypertension and diabetes, as well as education and counselling on healthy behaviours aimed to prevent CVD. The central strategy of this integrated approach is the use of total cardiovascular risk assessment to stratify and target individuals at high CVD risk, a process considered to be a ‘best buy’ intervention by WHO.^5^

These interventions are aimed at tackling areas identified in a 2014 WHO assessment of challenges and opportunities for better NCD outcomes in MDA.^13^ This includes shortcomings among health workers in the identification and management of individuals with increased cardiovascular risk. The interventions are expected to add to the current quality of care by targeting interventions (non-pharmacological and/or pharmacological) to those at highest risk who stand to gain the most in absolute cardiovascular risk reduction, while also emphasising improvements in the organisation of care. The intervention also includes practical face-to-face training and follow-up implementation support. Current practice underuses these medical strategies and guidelines (eg, CVD risk score directed primary prevention), in addition to limited task sharing with non-physician health workers (eg, nurses) in these care pathways.^13^ At the study’s inception, there were no known developments beyond the scope of this project that could change clinical practice for NCDs in primary healthcare.

Since the use of WHO PEN was unprecedented in MDA, the Ministry of Health, Labour and Social Protection convened a national steering group to lead the adaptation and pilot process, with the goal of using the findings for future health systems development. Led by the primary healthcare division of the Ministry of Health, the steering group comprises representatives from the Nicolae Testemitanu State University of Medicine and Pharmacy and the National Public Health Agency. The national steering group is supported by an international team of experts coordinated jointly by the WHO Regional Office for Europe and WHO Country Office in MDA.

## Aim and objectives

### Aim

The aim of the evaluation is to determine the feasibility of implementing and evaluating essential interventions for the prevention of cardiovascular disease in primary healthcare in MDA, with a view towards national scale-up.

### Objectives

#### Primary objectives

Assess the ability to implement MDA-adapted WHO PEN protocols 1 and 2 in pilot primary healthcare centres.Determine the feasibility of collecting quantitative data required for future studies of effectiveness from the existing informal paper clinical record system.

#### Secondary objectives

Determine the baseline performance of primary healthcare services with respect to essential interventions for the prevention and management of CVD.Estimate the change in performance of pilot primary healthcare centres after 12 months of protocol implementation and compare this with control clinics using usual care.

## Methods and analysis

### Overview of process and design

An overview of the methods used to adapt, pilot and evaluate essential interventions for CVD in primary healthcare in MDA are summarised by the following seven steps, which are planned to occur from September 2016 to May 2019.

#### Step 1: adaptation of WHO PEN protocols to the national context

Under the direction of the national steering group, WHO PEN protocols 1 and 2 will be compared and contrasted to national disease-specific guidelines. The WHO PEN protocols will then be adapted to ensure consistency with the organisation, culture and availability of resources of the health system, while ensuring that they remain simple clinical decision support tools.

#### Step 2: development of a training package for primary healthcare workers

A 3-day training package will be developed under the direction of the national steering group in order to provide in-person theoretical and practical training to nurses and doctors working in primary healthcare. This will include lectures, clinical case studies and practical exercises that embrace the experience and knowledge of participants.

#### Step 3: collection of baseline data

According to the Ministry of Health process, a list of 20 primary healthcare clinics will be nominated and provided to the working group. They will then be randomised into an intervention group arm (n=10) and control arm (n=10). Data for quantitative indicators will be extracted from all 20 clinics by randomly sampling individual paper-based patient records from all primary healthcare units using a standardised data collection instrument. This will be done before randomisation by a specially trained group of postgraduate medical trainees, such that neither the clinics nor the data extractors will know the allocation of each clinic to intervention or control arm.

#### Step 4: training staff in pilot clinics

All doctors and nurses from the primary healthcare centres in the intervention arm will be invited to be trained together by a national team of experts in groups of approximately 30. It is estimated that up to 200 health workers will be trained in total. At the end of training, each primary healthcare team will pass through evaluation at the University Centre for Simulation in Medical Training using objective structured clinical exams and get feedback from trainers and peers.

#### Step 5: implementation of protocols

Trained participants from the 10 primary healthcare clinics in the intervention arm will then be free to implement the clinical protocols and change their clinical practice, without incentives, for 12 months. During this time, a team of national experts will be created to offer support (distance and on-the-job) to the primary healthcare centres in the intervention arm. All 10 clinics in the intervention arm will receive at least one in-person follow-up support visit.

#### Step 6: collection of follow-up data

After 12 months, using the same method and data collection instruments used to collect baseline quantitative data (step 3), data will again be extracted from randomly selected individual paper-based patient records from all 20 healthcare centres. Five primary healthcare centres from the intervention arm will be selected by the national steering group for one-on-one semi-structured interviews with health staff. This will be supplemented by inviting a selection of staff from all 10 health centres in the intervention arm to participate in focus groups. Together, these qualitative data will be analysed thematically for explanatory themes.

#### Step 7: evaluation of results and sharing experience

The findings of the quantitative and qualitative analyses will be integrated in a final report and shared with key stakeholders, including health staff from the participating primary healthcare centres. The results will also be shared at a national conference and in an open-access peer-reviewed journal, in order to inform the future development of primary healthcare capacity in MDA.

### Methodological design

A pragmatic, sequential mixed methods explanatory design, composed of quantitative and qualitative strands of equal weight, will be used (figure 1). This design was chosen because it allows for the use of qualitative data to enlighten and explain the quantitative findings, including but not limited to the feasibility of collecting data from paper-based records, the contextual factors affecting guideline implementation, changes in clinical practice and optimisation for the future.

**Figure 1 F1:**
[figure not shown]
Illustration using the GATE frame structure^15^ of the mixed methods evaluation design. GATE, Graphic Appraisal Tool for Epidemiological studies.

A sample size of 20 primary healthcare centres was chosen because it was seen as a good balance of allowing for variation in clinic geography and demography, while still remaining feasible for the pilot implementation. Half of the centres (n=10) will be randomly allocated to the intervention arm and half (n=10) to the control arm. Baseline data will be collected from both intervention and control clinics, ensuring that baseline data are collected before implementation occurs.

Within clinic comparisons will be used to compare the 12 months before randomisation with the 12 months of implementation. Between clinics comparison will be used to compare the intervention clinics with control clinics during the same time period.

### Eligibility criteria for primary healthcare centres

Health facilities will be nominated by the Ministry of Health for participation based on the following eligibility criteria^1^: primary healthcare facilities must be operating in the public sector as legal entities^2^; primary healthcare facilities must be sampled in a way such that they are geographically distributed evenly across the country; equally from the Central, North and Southern regions of MDAand^3^ health facilities must be primary healthcare centres that are managed by family doctors with no specialist doctors working in the facility. These criteria were chosen in order to select a group of clinics that sufficiently reflect the majority of primary healthcare facilities in MDA.

### Randomisation

The clinics will be stratified based on the ratio of patients to family doctors to minimise possible confounding by doctor caseload, and then randomised electronically into two groups of 10 primary healthcare centres.

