#### Method of randomly sampling patient records

A random sample of the records of patients aged over 18 years, who have visited the medical facility within the past 12 months, will be taken. Since medical records in MDA are organised alphabetically on shelves, we created a randomly generated list of alphanumeric combinations that allowed for the selection of patient charts at random. For example, an alphanumeric code of ‘C24’ would correspond to the 24th patient chart in the section of last names starting with the letter C.

The list will be followed in the order that it was generated so as to prevent selection bias. The randomly selected chart will then be checked to see if it meets two inclusion criteria^1^: the patient is aged 18 years or older and^2^ the patient visited the health centre within the last 12 months. If the record meets these criteria, data will then be extracted. If it does not, it will be returned to the shelf and the next alphanumeric code on the randomly generated list will be used. This process will be repeated in each clinic until a sample size of 1.2% of the patient population in each clinic is sampled. This proportion was chosen pragmatically such that the average sample per primary healthcare centre would equal 100 unique patients.

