#### Data analysis

The change in indicators from baseline to follow-up will be calculated for intervention clinics and compared with control clinics (table 1). Subgroup analysis by age, gender and other demographic features may be done as deemed appropriate by the national steering committee. All analyses will account for stratified sampling. Since the health centre is the unit of inference for the outcomes (eg, health centre proportion of eligible patients with a documented CVD risk score), use of an intracluster correlation coefficient is not required for analyses of these outcomes. Age-adjusted and gender-adjusted logistic regression models will be used to analyse the differences in predefined indicators between intervention and control clinics and between baseline and follow-up. The differences in means of continuous variables between the intervention and control clinics and baseline and follow-up will be analysed using age-adjusted and gender-adjusted analysis of variance.

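### Baseline indicators are in hand before randomisation but not used in the draw; with 10 clinics per arm, balancing on a few and adjusting for clinic baseline would cut chance imbalance at low cost

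*Protocol article*

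**What the plan says.** Under Randomisation, the protocol article gives the whole allocation rule. "The clinics will be stratified based on the ratio of patients to family doctors to minimise possible confounding by doctor caseload", and they are then "randomised electronically into two groups of 10 primary healthcare centres". No other balancing factor is named, neither region nor any indicator. The number of strata and their cut-points are not given.

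Under Step 3, "Data for quantitative indicators will be extracted from all 20 clinics by randomly sampling individual paper-based patient records". That paragraph mentions randomisation first, but it states the order plainly: "This will be done before randomisation by a specially trained group of postgraduate medical trainees".

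Under Method of randomly sampling patient records, 1.2% of each clinic's patients are sampled. "This proportion was chosen pragmatically such that the average sample per primary healthcare centre would equal 100 unique patients". Step 6 draws records at random again at follow-up.

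Under Data analysis, baseline is used in one way: "The change in indicators from baseline to follow-up will be calculated for intervention clinics and compared with control clinics". For the regressions, "Age-adjusted and gender-adjusted logistic regression models will be used to analyse the differences in predefined indicators"; the clinic's own baseline value is not a named covariate. Methodological design also plans a comparison of the two arms over the same period. The unit is the clinic: "Since the health centre is the unit of inference for the outcomes".

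The comparison with control clinics is a secondary objective. The primary objectives concern feasibility, and the article says that the sample size was not chosen for power.

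**The concern.** The allocation is a single draw over 20 known clinics, made after their records have been read. A clinic's baseline value of an indicator is usually the best available predictor of its follow-up value. The plan balances instead on caseload, which bears on performance only indirectly.

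Because the clinic is the unit, balance depends on 10 against 10 units, not on about 2,000 records. Noticeable baseline differences on some of the 14 indicators in Table 1 are therefore likely. They cost precision, and they make a pilot meant to inform national scale-up harder to read. A later analysis plan can add a covariate, but it cannot alter an allocation already drawn.

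**Working it through.** The article gives no imbalance, power or between-clinic figure to reproduce. Results are therefore in between-clinic SD units, and quantities not in the article are marked as assumed.

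**1. Size of chance imbalance.** Input: 10 clinics per arm (Randomisation).
- SD of the difference in arm means = sqrt(1/10 + 1/10) = 0.447. The 95% range is ±1.96 × 0.447 = ±0.88.
- P(|difference| > 0.5 SD) = 2 × [1 − Φ(0.5/0.447)] = 0.264. P(> 1 SD) = 0.025.
- In percentage points, with 100 records per clinic, an assumed mean of 30% and an assumed intracluster correlation (ICC) of 0.05 to 0.20: clinic variance = p(1−p)[ICC + (1−ICC)/100]. At ICC 0.05 this is 0.21 × 0.0595 = 0.0125, so the clinic SD is 11.2 points and the 95% range is ±1.96 × 0.447 × 11.2 = ±9.8 points. At ICC 0.20 it is ±18.3 points.

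**2. What caseload stratification does.** Simulation (4,000 runs; 2, 5 or 10 strata). The chance of an imbalance above 0.5 SD is 26% if caseload is unrelated to the baseline indicator, 24% at correlation 0.3, and 19% to 23% at correlation 0.5.

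**3. What the planned comparisons leave.** Let d be the baseline imbalance and r the clinic-level correlation between baseline and follow-up (assumed; equal variances at both times). The error carried into the arm difference is:
- follow-up only: r × d
- change from baseline: −(1−r) × d
- adjusted for clinic baseline: about 0

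For d = 0.5 SD:

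| r | Follow-up only | Change |
|---|---|---|
| 0.3 | +0.15 | −0.35 |
| 0.5 | +0.25 | −0.25 |
| 0.7 | +0.35 | −0.15 |
| 0.9 | +0.45 | −0.05 |

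About 100 records per clinic, sampled afresh at follow-up, lower the r that applies to observed clinic values.

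**4. What a constrained draw gains.** There are C(20,10) = 184,756 allocations before stratification. Simulation: two caseload strata of 10 (assumed), four baseline variables, the best 200 of 2,000 stratified allocations kept. The imbalance SD falls from 0.45 to 0.19, so the imbalance variance falls by 1 − 0.19²/0.2 = 0.82. A separate simulation gave 0.15 with three variables and 0.22 with five, which brackets this.
- Follow-up only: the baseline share of the variance is r², so the reduction is 0.82 × r² = 20%, 40% and 52% at r = 0.5, 0.7 and 0.8. Direct simulation gave 19%, 39% and 53%.
- Change: the variance is proportional to 2(1−r), of which (1−r)² comes from baseline. The reduction is 0.82 × (1−r)/2 = 20%, 12% and 8%.
- Adjusted for clinic baseline: the variance is inflated by about 1 + d²/(0.2 × 18). At the average d² of 0.2 this is 1.056, and at d² = 0.19² it is 1.010, so the constraint gains only about 4%. For d = 0.5 the adjustment costs sqrt(1 + 0.25/3.6) = 1.034, about 3% in standard error.

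**5. Measurement error.** Balancing on one to five indicators, the chance that the true imbalance still exceeds 0.5 SD is 0% to 1% without measurement error, 1% to 5% at reliability 0.85 and 4% to 10% at reliability 0.70.

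**The case against.** The strongest reply is that the plan already uses baseline: it compares change between arms, which subtracts baseline on every indicator and costs no parameter. That stands in part. A reader might infer that baseline imbalance passes untouched into the results, or that the 39% and 53% reductions apply to the planned change comparison. The article supports neither. Those percentages belong to an unadjusted follow-up comparison. For the change comparison the gain runs the other way, falling to 8% at r = 0.8. But a change score leaves −(1−r)d, and the same-period comparison has no such protection.

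A reader might also infer that imbalance could be prevented at no cost. It could not. Clinic baselines are measured with error, worse for indicators that rest on a subset of records, such as patients with existing CVD. Indicators left out of the score stay largely to chance. Whether these data can be obtained from paper records at all is a primary objective, so the draw would depend on data whose availability is under test.

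It is also fair to say that 20 clinics do not rule out adjustment: each indicator needs only its own baseline, one parameter, and a separate analysis plan may already name it. Finally, stratified randomisation is valid and unbiased on average, and the arm comparison is secondary in a pilot not sized for power. All of this limits the weight of the point. It does not remove it, because only the protocol can fix how the draw is made.

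**Conclusion.** The point holds as a low-cost improvement in precision. Baseline indicator data exist for all 20 clinics before the draw. The draw uses only caseload, and the regressions name only age and gender. Any one indicator has about a 1 in 4 chance of a baseline difference above 0.5 between-clinic SD, and the planned comparisons remove this partly (change) or not at all (same period).

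A constrained draw would reduce the variance by about 20% to 8% for the change comparison, and by about 19% to 53% for an unadjusted follow-up comparison, as r goes from 0.5 to 0.8. Once clinic baseline is a covariate, little further gain is left.

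The 0.45 and 26% follow from 10 clinics per arm and a normal approximation. The correlation, the ICC, the two strata and the independence of the balancing variables are assumptions. Nothing here is a contradiction in the article or a source of systematic bias.

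**What to change.** - **Randomisation section.** Keep the caseload strata. Within them, list the possible 10/10 allocations, score each on balance of one to four reliably measured baseline clinic values (for example completeness of risk factor measurement, hypertension control, clinic size), and draw one at random from the best-balanced 10% or so. Name the variables and the cut-off before the draw.
- **Data analysis section.** Adjust each indicator for the clinic's own baseline value. Carry the balancing variables into the model, or use a permutation test over the constrained set. If the constrained draw proves impracticable, the baseline adjustment alone secures most of the gain.

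**Cost.** A short program and a list of variables, with no extra data collection. The draw must wait until the baseline records from all 20 clinics are entered, checked and tabulated, and the constrained set of allocations must be kept for the analysis. The baseline adjustment costs one parameter per indicator.

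### Clinics are allocated within caseload strata, but the named models adjust only for age and gender, and it is unclear whether the allocation strata enter the analysis

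*Protocol article*

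**What the plan says.** **Allocation.** Under Methodological design, "Half of the centres (n=10) will be randomly allocated to the intervention arm and half (n=10) to the control arm". The Randomisation section gives the only stratification factor and its purpose: clinics are "stratified based on the ratio of patients to family doctors", so as to limit confounding by caseload.

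**Selection.** The eligibility criteria for centres require clinics to be taken "equally from the Central, North and Southern regions". The reason given for the criteria is that the clinics should reflect most primary care facilities in the country. Region is not mentioned in the Randomisation section.

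**Analysis.** The Data analysis section compares change from baseline to follow-up between arms. For binary indicators, "Age-adjusted and gender-adjusted logistic regression models will be used to analyse the differences in predefined indicators between intervention and control clinics". Continuous variables "will be analysed using age-adjusted and gender-adjusted analysis of variance". Neither sentence names caseload or region. The same paragraph says that all analyses will allow for stratified sampling, without naming a stratum. The section on sampling patient records describes random selection of charts within each clinic, up to 1.2% of its patients, and names no other stratum.

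**Timing.** Baseline extraction comes first (Step 3): "This will be done before randomisation by a specially trained group".

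**The concern.** The article gives confounding as its reason for stratifying by caseload, so it regards caseload as a factor that may predict the indicators. A factor used to restrict the allocation belongs in the comparison of arms. The analysis then reflects the design, and whatever precision the stratification bought is kept. The model sentences do list covariates, and the one allocation factor is not among them. The sentence that might bring it in speaks of sampling, whereas the stratification is in the allocation. Two analysts could read it differently and fit different models.

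Region is a separate and lesser matter. It governs which clinics enter the study but neither how they are allocated nor how they are analysed. With 10 clinics per arm, chance can place noticeably more clinics of one region in one arm.

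What is at stake is the precision and reproducibility of the secondary objective that compares change in the pilot clinics with change in the control clinics. The primary objectives, on implementation and on the feasibility of data collection, are not touched.

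**Working it through.** The article states no power, alpha or powered sample size, so there is no figure of its own to reproduce.

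**1. Factors side by side**

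| Factor | Selection | Allocation | Named models |
|---|---|---|---|
| Caseload (patients per family doctor) | no | yes | not named |
| Region | yes | no | not named |
| Age, gender | no | no | yes |

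**2. Cost of adding the caseload stratum.** In a clinic-level comparison of 20 clinics, two arm means leave 20 − 2 = 18 degrees of freedom. With S strata as a factor, 20 − 2 − (S − 1) = 19 − S remain. The article does not give S, so a range is shown:
- S = 2: 17
- S = 5: 14
- S = 10 (pairs): 9

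With S = 2 and region added (2 more), 17 − 2 = 15 remain. The two-sided 5% critical t then goes from 2.10 (18 df) to 2.13 (15 df).

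**3. Possible gain.** Suppose the clinic-level terms explain 10% to 30% of the variance of clinic-level change (assumed; the article gives no figure). In a clinic-level linear analysis the standard error is then multiplied by √0.90 = 0.95 to √0.70 = 0.84. This does not carry over to a patient-level logistic model.

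**4. Regional balance under the stated allocation.** An even three-way split of 20 is not possible (20/3 = 6.67), so 7/7/6 is assumed. The number of 10:10 allocations is C(20,10) = 184,756.
- Best balance (4:3, 4:3 and 3:3 in either direction): the intervention arm receives (4,3,3) or (3,4,3) clinics. Count: 2 × C(7,3) × C(7,3) × C(6,3) = 2 × 35 × 35 × 20 = 49,000. Share: 49,000/184,756 = 26.5%.
- Also allowing 4:2 in the six-clinic region adds (3,3,4) and (4,4,2): 2 × 35 × 35 × 15 = 36,750. Total: 85,750, or 46.4%.
- Some region differing by 3 or more clinics (5:2 or worse among seven, 5:1 or worse among six): 1 − 0.464 = 53.6%.
- Some region differing by 4 or more: 20.2%.
- A region absent from one arm: 1.6%.

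In simulations of 100,000 allocations with caseload strata of 10, 4 or 2 clinics, unrelated to region, the chance of a difference of 3 or more was 53.5%, 53.5% and 53.6%. Stratifying on an unrelated factor does not help regional balance.

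For an 8/6/6 split all differences are even. The chance of 2 or more is 84.8%, and of 4 or more 31.4%.

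**5. Room left by a region constraint.** With two caseload strata of 10 (assumed), C(10,5)² = 252² = 63,504 allocations exist. If caseload is unrelated to region, about 26.5% of them, some 16,800, also meet the limit of 4:3, 4:3 and 3:3. Allocation would stay unpredictable.

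**The case against.** **The strata may already be meant.** A reader might infer that the allocation stratum is left out of the analysis. The document does not support so firm a statement. Caseload is the only stratification the article names explicitly, so the sentence on stratified sampling may be a loose reference to it. The article is also condensed, and full covariate lists often sit in a fuller document. This stands in part: the finding is lack of clarity, not proven omission. But the article does list covariates, in two sentences, and the stratum is in neither.

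**Region is a preference.** A reader might infer that allocating without regard to region is an error that probably biases the result. The document does not support that either. Even selection is justified by representativeness, no passage shows that region predicts change, and chance imbalance is a normal property of randomisation. Comparing change from baseline removes stable regional differences in level. What remains is regional difference in trend or in response. The between-clinic comparison under Methodological design would lack that protection if it were made on follow-up levels. The 53.6% also assumes that caseload is unrelated to region. The Introduction says that doctor density is halved in rural areas, so caseload varies with geography. If it tracks region, the strata would partly balance region.

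**Standard errors.** It is tempting to say that leaving out the stratum makes standard errors too wide. That holds only for a clinic-level linear analysis. If the logistic models were fitted to patients with no clustering term, standard errors would be too narrow. In logistic regression, adding a prognostic covariate also does not generally shrink the standard error of the log odds ratio.

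**Weight.** This is a feasibility pilot sized on pragmatic grounds, and the arm comparison is a secondary objective. That stands and limits the importance of the point.

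**Conclusion.** The point holds for caseload. Allocation is stratified on it, the named models adjust for age and gender only, and the sentence on stratified sampling does not clearly bring the allocation strata in. Naming the stratum is a specific and nearly free improvement: one degree of freedom if there are two strata, more if there are more. The gain in precision cannot be stated, because the article gives no between-clinic variance and does not settle the level at which the models are fitted.

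The point on region is optional. Moderate imbalance is more likely than not (53.6% for a difference of 3 or more clinics in some region), given the assumed 7/7/6 split and independence of caseload and region. Severe imbalance is not: 20.2% for 4 or more, and 1.6% for a region absent from one arm. Since change from baseline is compared, the remaining risk is confined to regional differences in trend or response.

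**What to change.** **Data analysis section (recommended).** State that the between-arm analysis of change includes, as a clinic-level term, the caseload stratum used in the randomisation. Reword the sentence on stratified sampling so that it says this, and describe the sampling of records within clinics separately. The cost is two sentences of text and one degree of freedom per stratum beyond the first.

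**Region (optional).** Add region as a clinic-level term in a sensitivity analysis, at a cost of 2 degrees of freedom. If allocation has not yet been done, region can instead be a balance constraint: list the allocations balanced on the caseload stratum, keep those with regional splits of 4:3, 4:3 and 3:3 (or the equivalent for the actual numbers), and draw one at random electronically. All 20 clinics are known and their baseline records extracted before randomisation, so this needs only a short allocation script. Before the caseload restriction, the limit leaves 49,000 of 184,756 allocations. If allocation is already complete, only the analysis changes apply.
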